## Abstract

**Background:**

Mindfulness meditation (MM) is a commonly used psychological intervention for pain, mood, and anxiety conditions, but can be challenging to practice with severe symptoms without proper training. The Mindfulness Meditation app (MMA) is a supportive training tool specifically developed for this study to aid in the practice of mindful breathing using a smartphone.

**Objective:**

This study aims to evaluate the psychophysiological effects of the MMA. Specifically, the study will assess parasympathetic functioning using heart rate variability (HRV; primary outcome), pain and mood symptoms, mind-wandering and present moment awareness, and breath focus in groups of undergraduate participants who self-report clinically-relevant symptoms of chronic pain (CP) and depression or anxiety (DA) and condition-free (CF) participants who do not meet either criteria. We hypothesize that use of the MMA by study groups will lead to improved HRV, pain, and mood symptoms compared with groups who do not use the app.

**Methods:**

This study is a two-arm randomized controlled trial (RCT) recruiting through a Web-based research participation pool at York University in Toronto, Canada. We are aiming for minimum 60 participants in each of CP, DA, and CF groups. Upon arriving to the laboratory, participants will be prescreened for classification into groups of CP, DA, or CF. Groups will be randomly assigned by a 1:1 ratio to an MMA (MMA+) condition or MM condition without the app (MMA−) after a brief stress induction procedure. In MMA+, participants will practice mindful breathing with a smartphone and press breath or other buttons at the sound of audio tones if their awareness was on breathing or another experience, respectively. HRV and respiration data will be obtained during rest (5 min), stress induction (5 min), and meditation conditions (12 min). Participants will complete psychological self-report inventories before and after the stress induction and after the meditation condition. Separate linear mixed models will be used to examine HRV and self-report inventories comparing groups and treatment conditions.

**Results:**

Recruitment for the study began in November 2017 and is expected to be completed in winter of 2019-2020. As of July 2019, 189 participants have been recruited. The study’s main findings are expected to reveal a positive pattern of HRV responses in the CP, DA, and CF groups, such that a significant increase in HRV (*P*<.05) is detected in those randomized to the MMA+ condition in comparison with those randomized to the MMA− condition.

**Conclusions:**

This RCT will contribute to the burgeoning health psychology literature regarding the clinical relevance of HRV in assessment and treatment of psychological and medical conditions. Furthermore, possible ways to inform designs of MM training tools delivered by apps and Web platforms for CP, depression, and anxiety conditions’ treatment will be discussed.

**Trial Registration:**

Clinicaltrials.gov NCT03296007; https://clinicaltrials.gov/ct2/show/NCT03296007.

**International Registered Report Identifier (IRRID):**

DERR1-10.2196/14119

## Introduction

### Background

Mindfulness meditation (MM) is an element of the Buddhist traditions first introduced as a clinical intervention in western medicine by Kabat-Zinn [1]. Over the past 35 years, the practice has received significant interest in clinical and health psychology and, more recently, in neuro- and psychophysiology. A family of meditative practices based on mindfulness is commonly used as a psychological approach to mental illness and chronic pain (CP) management. Mindful breathing is central to the mindfulness practices and places an emphasis on paying nonjudgmental attention to one’s cognitive, emotional, and physical experiences while reorienting focus on breathing sensations to cultivate cognitive and emotion regulation and progressively relaxed states [2]. Mindfulness-based treatments have been shown to be effective in reducing symptoms of depression, anxiety, and chronic pain [3,4].

One proposed mechanism for mindful breathing benefits is the state relaxation effect mediated by parasympathetic vagus nerve activation because of its process of bringing awareness to breathing sensations while practicing acceptance of stressors such as worrying thoughts, negative emotions, and pain [5]. However, individuals with pain, depression, and anxiety disorders commonly share the physiological trait of a dysregulated autonomic nervous system (ANS), particularly with respect to parasympathetic stress recovery processes, which compromise vagal activation [6,7].

Rigid and inflexible types of mind wandering, such as worry and rumination, are typically seen in individuals with psychiatric illnesses [8,9] and chronic pain [10]. These stressors lead to prolonged physiological stress activation linked to health risks [6,11]. MM attempts to counteract unhealthy mind wandering by instilling present-oriented attention that is more conducive to appropriately rested and relaxed states in the absence of stressful demands [12]. Critical to the purported benefits of mindfulness is that the removal of stressful stimuli in the environment does not always coincide with a return to resting state. Physiological stress inevitably arises through pain, worry, rumination, and distressing emotions such as fear, anxiety, and anger. Patterns of worry and rumination are defined as *perseverative stressors*, as they are typically related to past or anticipated stressors [6]. Perseverative stress refers to persistent physiological stress that can linger for prolonged periods, sometimes subconsciously, creating an undertone of stress arousal and allostatic load associated with gradual and sustained withdrawal of vagal tone, quantifiable by low heart rate variability (HRV) [11]. Chronically low HRV is a sign that the ANS is *sympathetically dominant*, with persistent and excessive activation of the stress response that is less amenable to vagal-mediated parasympathetic recovery [6,11]. Mindfulness practice may be a key method to target the pathophysiological mechanism common to chronic pain, depression, and anxiety. Mindful breathing can enhance vagal activation through state relaxation effects, as multiple studies have shown that even brief mindfulness practice after stress significantly increases HRV [13,14]. This vagal-activating effect may have stress-relieving benefits for individuals with depression-anxiety symptoms [15]. With regards to pain, reductions in self-reported pain have been demonstrated in individuals practicing HRV-based biofeedback [16], and it has been theorized that increased vagal activation is connected to several analgesic mechanisms such as lowered systemic inflammation and inhibited pain-processing brain regions [17]. Thus, the vagal-activating treatment potential of a smartphone-based mindful breathing app may have clinical utility, given the strong research evidence associating low HRV and psychological [18] and pain conditions [7].

A potentially impeding factor for client populations in practicing mindful breathing is the demand characteristics of the silent, inwardly focused exercise that may naturally make them more saliently aware of their symptoms of depression (eg, rumination), anxiety (worry), and pain (sensations). Relatedly, a qualitative study has revealed experiential challenges to MM practice that must be addressed in clinical treatment contexts, including the fact that meditation is a difficult skill to learn and practice, and participants encounter difficult thoughts and feelings amidst practice [19]. This is all the more relevant to naïve meditators with pain, depression, and anxiety symptoms, making for a potentially challenging experience that discourages further MM practice.

Supportive training tools, such as smartphone apps, are widely used to receive audio guidance on MM, and evidence is emerging for their immediate and long-term effects on altering mood states [20]. However, few studies have investigated the clinical utility and physiological changes related to meditation-based smartphone apps [21]. Furthermore, audio instructions may not be readily applicable in participants with clinical symptoms as they may be more vulnerable to their mind-wandering effects amidst meditation practice. In 1 study, a computer-based mindful breathing task provided random audio tones during the practice to prompt participants to reorient attention to breathing sensations after pressing a button on the keyboard to indicate whether they had been paying attention to breathing or other experiences at the time of the tone [22]. The results showed higher instances of breath attention were correlated with increased HRV during the practice, suggesting a positive relaxation effect of the mindful breathing task. This paradigm could be effectively applied in a clinical context for individuals who may initially struggle to practice mindful breathing, such as those with chronic pain and severe depression-anxiety symptoms. Although multiple studies have shown that MM leads to HRV increases [13,22], there are no known studies that have investigated the effects of a smartphone-based mindful breathing task on HRV in individuals with chronic pain and severe depression-anxiety symptoms. One study provided naïve meditators training in the mindfulness technique of thought distancing using a smartphone app or traditional mindfulness practice without an app. They found significantly greater mindfulness and pleasantness and lower perceived difficulty associated with the smartphone app–based mindfulness practice compared with the nonapp conditions [23]. More investigations are needed to determine in what ways smartphone apps can be employed as an effective medium of delivering mindfulness training to vulnerable populations who are naïve to meditation.

A recent systematic review of mindfulness-related apps found over 500 apps in the marketplace, but only 23 were designed to provide mindfulness training, and they were largely focused on providing audiovisual guidance, timers, and reminders to practice [21]. The review revealed that only 1 randomized controlled trial (RCT) for a mindfulness app was underway at the time [24] and that, generally, there is limited evidence available for the efficacy of apps in increasing mindfulness [21]. Furthermore, the literature on existing mobile apps marketed for chronic pain reveals that, with few exceptions [25], they rarely adhere to scientific guidelines and that health care professionals are rarely involved in their development [26-29].

The aim of this study is to overcome some of the aforementioned limitations by designing an app with input from clinical researchers and empirically testing the app’s effectiveness in a sample of young adults with CP, anxiety, and depression. To cultivate mindfulness, a mobile-based Mindfulness Meditation app (MMA) was developed based on Burg et al’s [22] mindful breathing exercise that “assesses the participants’ ability to mindfully stay in contact with the bodily sense of the breath during an exercise aligned with breathing meditation” [22]. In lieu of verbal meditation instructions amidst practice, the task provides audio tones at random intervals to which practitioners respond by pressing keys to indicate *breath* (if they were attending to their breathing at the sound of the tone) or *other* (if they were attending to an experience other than the breath at the sound of the tone). This simplified task may be more suitable to beginner meditators and particularly those with various psychiatric and pain symptoms that make meditation practice more difficult [19]. In a previous pilot study of the MMA ([name], MA, unpublished data, June 2017), participants with chronic pain and severe depression-anxiety symptoms randomized to the 12-min MMA task exhibited significant reductions in mood states of anxiety, anger, and overall distress.

This study will evaluate the psychophysiological effects of a smartphone-based MMA (12 min; Figure 1) for individuals with clinically significant symptoms of major depression or anxiety (DA) or chronic pain. Specifically, the study aims to examine parasympathetic activity using HRV (primary outcome) in groups of participants who self-report clinically significant symptoms of DA and CP and condition-free (CF) participants who do not meet our criteria for either. In addition, given the linkages between HRV and the following psychological processes within psychological and medical conditions, the study will also assess mind wandering and present moment awareness, mood symptoms, and breath focus before and after the intervention. All study groups will be randomized to an MMA (MMA+) condition or a MM condition without the app (MMA−) after a brief stress induction procedure.

Overall, 3 major hypotheses (1a, 1b, 2a, 2b, and 3) will be tested.

**Figure 1 figure1:**
[figure not shown]
The Mindfulness Meditation App.

### Primary End Point

#### Hypothesis 1a

HRV change scores during MM will be significantly higher in the CP and DA groups receiving MMA+ compared with corresponding CP and DA groups receiving MMA−, and will not differ between CF groups receiving MMA+ or MMA−.

#### Hypothesis 1b

HRV will significantly increase from the stress to MM phases in CP and DA participants receiving MMA+ compared with corresponding CP and DA groups receiving MMA−, and will not differ between CF groups receiving MMA+ or MMA.

### Secondary End Points

#### Hypothesis 2a

CP and DA participants randomized to MMA+ will report significant pre-post increases in levels of present moment awareness and state mindfulness compared with participants randomized to MMA−, and present moment awareness and state mindfulness will not differ between CF groups receiving MMA+ or MMA.

#### Hypothesis 2b

CP, DA, and CF participants receiving MMA+ will report significantly lower mind wandering than corresponding participants receiving MMA−, reflecting the potential for MMA+ to make participants more able to recover their attention from mind-wandering contents and processes during MM.

#### Hypothesis 3

CP and DA participants randomized to the MMA+ condition will demonstrate significant reductions in mood symptoms (state depression and anxiety) after the MM task compared with CP and DA participants randomized to the MMA− condition, reflecting the potential for MMA+ to facilitate the emotion regulation effects of MM for clinical populations.

## Methods

### Design

This RCT study was designed according to the 2010 Consolidated Standards of Reporting Trials statement (Multimedia Appendix 1) [30], reviewed and approved by the York University research ethics board (Human Participants Review Committee protocol number e2017-303), and registered with ClinicalTrials.gov (NCT03296007) on September 22, 2017, before the recruitment of the first participant. A total of 180 male and female participants will be recruited from the Web-based York Undergraduate Research Participant Pool, based on voluntary participation, and classified into 3 groups of approximately 60 participants each (and randomized into MMA+ or MMA−) based on their prescreening questionnaires: CP (n=30 MMA+ and n=30 MMA−), depression-anxiety (n=30 MMA+ and n=30 MMA−), and CF participants (n=30 MMA+ and n=30 MMA−; Figure 2).

**Figure 2 figure2:**
[figure not shown]
Consolidated Standards of Reporting Trials 2010 flow diagram showing anticipated participant flow for enrolment, group classification, randomization to intervention, and analyses. MMA−: mindful breathing practice without using the Mindfulness Meditation app; MMA+: mindful breathing practice using the Mindfulness Meditation app; TBD: to be determined.

### Sample Size Estimation

Sample size estimate for a repeated-measures linear mixed-effects analysis of variance (ANOVA) with 3 groups (CP, DA, and CF), 2 conditions (MMA+, MMA−), and 3 phases (baseline, stress induction, and MM) indicates that a total of 141 participants are needed to detect small-to-medium effect size (f=0.15) HRV changes with a type I error rate (alpha) of .05, a power of 0.95, and a 0.50 correlation between repeated measures (G*Power; Heinrich Heine University Düsseldorf). The small-to-medium effect size corresponds to previously published studies of HRV increases during brief mindfulness practice [13,14]. Recruitment of more than 180 participants will allow for an attrition rate of approximately 20% because of withdrawals, dropouts, technical failures, and missing data. On the basis of prescreening and recruitment numbers in our past pilot study ([name], MA, unpublished data, June 2017), we found the percentage of participants reporting diagnosed CP, severe depression, or anxiety symptoms to be 27%, 33%, and 41%, respectively. Accordingly, the combined number of students expected to be prescreened for eligibility to enroll 60 participants per group will be approximately N=550.

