### Control Arm: Mindfulness Meditation With No App

Participants in the MMA− condition will engage in mindful breathing without use of the smartphone app for 12 min in a seated and eyes closed position.

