## Discussion

### Principal Findings

The main findings of the study are expected to reveal a positive pattern of HRV responses across the different study groups, CP, DA, and C, such that they exhibit significantly increased HRV (*P*<.05) in the treatment condition, MMA+, in comparison with the control condition, MMA−. On the basis of previous research published by our team, HRV is expected to increase during MM when practiced after stressor tasks [13,14]. However, a pattern of *inflexible* HRV responses has been noted in previous studies involving participants with clinical characteristics. For instance, a randomized experimental study of students high on perfectionistic traits and nonperfectionist students was conducted with measurement of HRV at baseline, stress, and during subsequent audio-guided MM or a rest condition with an audio lecture. Only the nonperfectionist group exhibited significantly increased HRV in the mindfulness condition, whereas the perfectionists did not, reflecting an inflexible state of sympathetic dominance [13]. A follow-up study was conducted with headache and headache-free participants where both groups showed increased HRV during post-stress mindfulness. However, during post-stress rest, the headache group exhibited significantly lower HRV compared with headache-free participants, reflecting impaired ability for cardio-vagal recovery [14]. This pattern of results is consistent with literature indicating low and inflexible HRV patterns in individuals with clinical characteristics of depression, anxiety, and chronic pain [52-54].

The MMA is designed as a supportive training tool to aid clinical populations with mindful breathing practice. Accordingly, our primary hypothesis is that HRV will increase from the stress to MM phases in DA and CP participants randomized to MMA+ compared with MMA−. Specifically, mindful breathing practice with the aid of the MMA is expected to yield additional relaxation effects for participants, by way of respiratory sinus arrhythmia, to be reflected in increased HRV measures. Examination of secondary hypotheses will help to further contextualize the role of key psychological processes, including present moment awareness, state mindfulness, mind wandering, and mood, as mediators and outcomes of mindfulness-based treatments.

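### The stated 0.95 power rests on an HRV effect of mindfulness practice, which both arms receive, and does not apply to the planned MMA+ versus MMA− comparisons within each group

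*Protocol article*

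**What the plan says.** Sample Size Estimation describes a repeated-measures mixed-effects ANOVA with "3 groups (CP, DA, and CF), 2 conditions (MMA+, MMA−), and 3 phases (baseline, stress induction, and MM"). It "indicates that a total of 141 participants are needed to detect small-to-medium effect size (f=0.15) HRV changes". The other inputs are alpha .05, power 0.95 and a correlation of 0.50 between phases. The only support for the effect size is that "The small-to-medium effect size corresponds to previously published studies of HRV increases during brief mindfulness practice [13,14"].

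The question asked of the trial is different. The Abstract's Objective expects improvement in app users "compared with groups who do not use the app". Hypothesis 1a, one of two coprimary hypotheses, predicts larger HRV change with MMA+ than with MMA− in CP and in DA, and no difference in CF. Its analysis section plans the MMA+ versus MMA− comparison separately in each of the three groups. Control participants "will engage in mindful breathing without use of the smartphone app for 12 min in a seated and eyes closed position".

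Principal Findings in the Discussion describes the two studies cited for f. The first measured HRV at baseline, under stress, and "during subsequent audio-guided MM or a rest condition with an audio lecture". In the second, with headache and headache-free participants, "both groups showed increased HRV during post-stress mindfulness", and the groups differed during post-stress rest. The same section expects the app to bring relaxation beyond that of the breathing practice itself.

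**The concern.** An effect size used for sizing should belong to the contrast being tested. Here it is described as an effect of mindfulness practice. Since MMA− also practises mindful breathing, that component is common to both arms, and only what the app adds can separate them. The document gives no HRV effect size for that increment; the pilot study mentioned in the Background is cited for mood, not for an HRV difference between arms.

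A reader will naturally take 0.95 as the power for MMA+ versus MMA−. A null result in CP or DA could then be reported as showing that the app adds nothing, and a null result in CF as confirming the predicted absence of a difference. Neither conclusion would be backed by the design's actual sensitivity.

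**Working it through.** **Inputs from the protocol article.** Sample Size Estimation: f=0.15, alpha .05, power 0.95, correlation 0.50, 3 phases, N=141, about 20% attrition. Design: 60 per group, 30 per arm within group, 1:1. Results: 41 CP participants as of July 2019.

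**Step 1. Reproduce 141.** For a within-between interaction, λ = f²·N·m/(1−ρ). With N=141 and m=3, λ = 0.0225 × 141 × 3 / 0.50 = 19.04.

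| Term | df | N for 0.95 | Power at N=141 |
|---|---|---|---|
| Group × phase (3 cells) | 4, 276 | 140, or 141 with equal groups | 0.952 |
| Group × condition × phase (6 cells) | 4, 270 | 141 | 0.951 |
| Six cells × phase, one joint test | 10, 270 | 186 | 0.857 |
| Two arms × phase | 2, 278 | 116 | 0.980 |

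The plan's figure arises only from a 4-df interaction. In the first of these, the arm does not enter. In the second, f measures how the app effect varies between groups, not how large it is in any one group. Neither is the Hypothesis 1a planned comparison.

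**Step 2. Convert f=0.15 to that comparison, giving it full credit.** For two arms and two phases (stress and MM) at ρ=0.50, λ = f²·N·2/0.50 = 4f²N. A two-sample t-test on change scores has squared noncentrality d²N/4. Equating them gives d = 4f = 0.60.

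The conversion is slightly sensitive to form. With three phases and an arm difference at MM only, the interaction variance is d²/18, so d = 0.15 × √18 = 0.64.

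**Step 3. Power of the within-group comparison at d=0.60**, two-sided .05, noncentrality d·√(n/2):

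- 30 per arm: 0.60 × √15 = 2.32, 58 df, critical value 2.00, power 0.63.
- 24 per arm (30 × 0.8, the plan's own attrition): 0.60 × √12 = 2.08, 46 df, critical value 2.01, power 0.53.

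**Step 4. Detectable difference at 80% power, two-sided .05:**

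| Analysed within one group | Detectable d |
|---|---|
| 30 per arm | 0.74 |
| 24 per arm | 0.83 |
| 20 and 21 (CP at 41, before any loss) | 0.90 |

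Both conversions in Step 2 (0.60 and 0.64) lie below every entry.

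**The case against.** Four points deserve weight.

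- **Where f came from.** A reader might infer that f=0.15 was computed from mindfulness versus rest. The text does not say so: it says the value corresponds to published HRV increases, which could equally be a within-person rise. The contrast that gave 0.15 cannot be established from the document. This stands, but on either reading the effect is one of mindfulness, which both arms receive.
- **Whether the app's effect is smaller.** A reader might infer that it must be, because the control arm meditates too. The document does not establish this. The Introduction argues that silent practice may be hard for symptomatic beginners, and the Discussion reports that perfectionistic students did not raise their HRV under audio-guided mindfulness. If unaided practice does little in CP and DA, the app's increment could approach the full effect. This stands in full, so power is not shown here for assumed fractions of f, and the calculation above credits the app with all of it.
- **The three-way interaction is a relevant test.** Hypotheses 1a and 1b both expect an app effect in CP and DA but not in CF, and the 1b model contains that term. This is fair, but no cited evidence gives f=0.15 for it either, and it does not supply the power of the per-group comparisons.
- **Intervals are already planned.** Statistical Analyses of Outcomes commits to confidence intervals and effect sizes. The stated power is therefore not the only safeguard against over-reading a null. What is missing is a statement of how a null arm difference will be read.

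**Conclusion.** The concern holds in a limited form. The cited basis for f=0.15 concerns mindfulness practice, and nothing in the document links it, or the 0.95 power, to MMA+ versus MMA−. Separately, 0.95 at N=141 belongs to a 4-df interaction and not to the per-group arm comparisons of coprimary Hypothesis 1a. Granting f=0.15 in full between arms, those comparisons reach about 0.63 with 30 per arm and 0.53 with 24.

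These figures assume correlation 0.50, equal variances, a two-sided unadjusted .05 test in each group and the two-phase conversion to d=0.60. They do not say that the app's true effect is small. They say that the stated power does not describe the trial's primary comparison.

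**What to change.** In Sample Size Estimation:

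1. State that f=0.15 reflects HRV change with mindfulness practice, and that 0.95 power does not apply to the MMA+ versus MMA− planned comparisons.
2. Name the model term to which 141 and 0.95 refer.
3. Give the within-group arm difference in stress-to-MM change that is detectable at 80% power, two-sided .05: about d=0.74 with 30 per arm and d=0.83 with 24 per arm. Update it to the numbers actually analysed (about d=0.90 for CP at the 41 reported in Results, before any loss).

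In Statistical Analyses of Outcomes, add that a non-significant arm difference will not be read as absence of an app effect, and that the confidence interval already planned will carry the interpretation, including for the predicted null in CF.

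The cost is a less favourable stated power. Recruitment, procedures and data collection do not change, and no added participants are needed.
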